**Study setting.**

This study is to be carried out at the Kenyatta Hospital (KNH) antenatal and labor wars. KNH is the largest teaching and referral hospital in Kenya. It receives patients from Nairobi and its environs as well as referrals from all other hospitals in Kenya. It has a bed capacity of 1800 beds and is located 2km southwest of the Nairobi Central Business District.

Mothers will be recruited as they are admitted for delivery due to an indication that warrants induction of labor (WHO) which include

1. Postdates
2. Pre eclampsia.
3. Chronic hypertension.
4. Gestational diabetes.
5. Oligohydramnios.
6. Intrauterine Fetal Demise.

**Study population**

Pregnant women admitted for induction of labor at KNH at gestational age of 28 weeks and beyond.

INCLUSION & EXCLUSION CRITERIA:

Inclusion:

Intrauterine gestation, cephalic presentation, intact membranes, IUFD and Bishop score less than 6.

Willing to give informed consent.

Exclusion:

IUGR, Previous cesarean sections, multiple gestation, contraindication to prostaglandins, fetal anomalies, other uterine surgeries, EFW>4000G,Placenta previa, NRFS, multiparity >5,HIV infected and those not sure of dates by clinical examination as well as ultrasound dating.

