**SPECIFIC OBJECTIVES**

Among pregnant women undergoing cervical ripening and induction of labor using combined misoprostol and Foley balloon versus misoprostol alone,

1. Determine and compare the incidence of failed induction.
2. Determine and compare the induction to delivery time.
3. Determine and compare immediate maternal and perinatal outcomes.

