**METHODOLOGY**

**Study design**

Two arm open label (non blind) RCT

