**Outcomes**

Primary outcome-failed induction

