**Secondary outcome**

Induction to delivery time

Mode of delivery

Maternal outcomes-PPH, chorioamnionitis,hyperstimulation(5 contractions in 5mins)

Perinatal outcomes (APGAR, NICU admission

Methodology

Block randomization of all eligible consenting subjects by computer generated random sequences and a randomization ratio of 1:1.Upon enrollment, an opaque envelope containing the participant’s enrollment number and assignment to either the Foley plus vaginal misoprostol or vaginal misoprostol alone will be opened .Each participant will be assigned a unique 4-digit-long subject number for subject identity and confidentiality. Participants and health provider will be aware of the treatment allocation at the time of assignment of treatment.

Study procedures.

Patients who fall in the Misoprostol arm will be given 25 mcg vaginally 6hourly up to a maximum of 4 doses, Bishop score >6 or when they go into active labor. Later amniotomy and augmentation may be done as per protocol

Patients who fall in the Combination arm will be inserted an 18-French Foley catheter with a 30 cc balloon will be placed just above the internal cervical os and then inflated with 30 cc of sterile saline. The length of the Foley catheter will be affixed to the subject’s inner thigh under slight tension. At the same time 25 mcg of misoprostol is inserted at the posterior fornix of the vagina 6 hourly up to a maximum of 4 doses, Bishop score >6 or active labor. If difficult, Foley catheter insertion will be attempted every 6 hours unless Bishop score more than 6 or in active labor. When Foley balloon falls off, labor may be augmented or amniotomy performed as per the existing protocol.

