**Sample size calculation**

A recent Kenyan study placed failed induction at 26%.

We postulate that offering a combined use of misoprostol and Foley catheter will reduce this proportion to 16%.

Therefore for us to detect a 16% difference in the successful induction following the use of Foley with misoprostol versus misoprostol alone, we estimated using the sample size formula,

Sample size formula

[Allan Donner; Stat. Medicine (1984)

that we would need to study a total of 180 women (90 per group) to achieve a 80% power to detect the stated difference of 16% at a two-sided alpha=0.05 level of significance.

Where we define p_c_=74% and p_a_=90% to be the proportions of women in the misoprostol and combined misoprostol and Foley groups respectively

and = (p_C_ + p_a_)/2 ( =1.960, and =0.84

**Data collection, management and analysis**.

Data collection and storage: Data will be collected by use of questionnaires by the principal investigator and 3 or 4 well trained research assistants. Information will be obtained from history, review of medical records and clinical examination. The information will be stored safely in a password-protected computer and backed up on a dedicated USB drive. Any hard copy records carried for analysis will be stored under lock and key and patients confidentiality will be observed. A qualified statistician will do analysis as per protocol with intent to treat analysis using SPSS version 21.Primary outcome will be failed induction/successful induction and secondary outcomes include time to delivery, maternal and perinatal outcomes. Proportions will be compares using Chi2 test, 95% CI, two tailed hypothesis with p significant at <0.05

Ethical considerations.

- Permission will be sought from the KNH/UON ERC.
- Informed Consent.
- Confidentiality.
- Patients who decline to give consent will be treated as per the existing protocols and no penalty at all.

Study limitations

Non-blinding may have influence patient management

No long-term follow up of mother and neonate for late outcomes

No interim analysis due to resources.

Study timelines

- Proposal presentation-January 2014
- ERC approval and registration-February 2015
- Enrollment-march-September 2015
- Analysis-September-December 2015
- Presentation-December 2015
- Publishing-December-June 2016
- Dissemination of results-June 2016

Study budget

The anticipated expenses during this study include the following-

Buying of Foleys catheters and misoprostol-

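### NICU admission and Apgar are compared by an unstratified chi-square test from 28 weeks to postdates, losing precision that stratifying by gestational age at entry would recover

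*Protocol*

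**What the plan says.** - **Entry.** The second Study population section of the protocol admits "Pregnant women admitted for induction of labor at KNH at gestational age of 28 weeks and beyond". The limit applies to every indication, and the list under Study setting puts pre-eclampsia, chronic hypertension and oligohydramnios beside postdates. The same section excludes women whose dating is uncertain.
- **Outcomes.** The third specific objective is to "Determine and compare immediate maternal and perinatal outcomes". The Secondary outcome section lists "Perinatal outcomes (APGAR, NICU admission" and names no gestational-age subset. The analysis paragraph confirms their rank: "secondary outcomes include time to delivery, maternal and perinatal outcomes". The primary endpoint is failed induction.
- **Allocation.** "Block randomization of all eligible consenting subjects by computer generated random sequences and a randomization ratio of 1:1". No stratification factor is named.
- **Analysis.** The paragraph on data collection, management and analysis specifies intention to treat and a chi-square test for proportions, two-sided at 5%. It mentions no stratification or adjustment. The protocol does not say how Apgar will be split; once expressed as a proportion, it falls under this test.

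**The concern.** A live birth at 28-33 weeks probably has a much higher chance of NICU admission than one at 41 weeks, whichever ripening method is used. The protocol gives no rates, so this is an assumption, but a mild one. If it holds, much of the variation in NICU admission and Apgar is explained by a baseline value that the stated test ignores. That variation stays in the standard error and makes a difference between methods harder to see. The pooled rate in each arm is also an average over two very different groups of babies and applies to neither.

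Neonatal outcome is part of the trial's rationale: the Study justification says that failed or prolonged induction may harm the newborn. With 90 women per arm, sized for another endpoint, the perinatal comparison has little precision to spare.

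**Working it through.** **The plan's own figure.** The sample size is for the primary outcome, 74% versus 90% success. With mean 0.82, z-values 1.96 and 0.84:

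n = [1.96·√(2·0.82·0.18) + 0.84·√(0.74·0.26 + 0.90·0.10)]² / 0.16² = 89.2, so 90 per group.

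The stated 90 per group reproduces. It says nothing about NICU admission or Apgar, but it fixes the number available.

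**Inputs.** From the protocol: 90 per arm, 1:1, unstratified allocation, unadjusted chi-square, two-sided 5%. Assumed, because the protocol gives no values: preterm share q of 10-40%; NICU risk of 5-10% at term (pt) and 40-80% preterm (pp). All 90 per arm are treated as live at entry. Eligible intrauterine deaths would lower that number.

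**Is the pooled comparison biased?** Sixteen scenarios were simulated with 200,000 trials each. With no treatment effect, the mean difference between arms was at most 0.0003 in size, and the chi-square type I error was 4.8-5.1%. There is no bias.

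**How much precision is lost?** The share of outcome variance due to the preterm/term split is q(1−q)(pp−pt)² / [p(1−p)], where p = q·pp + (1−q)·pt.

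- q = 20%, risks 10% and 50%: p = 0.18; 0.16·0.40²/(0.18·0.82) = 0.17.
- q = 20%, risks 5% and 80%: p = 0.20; 0.16·0.75²/(0.20·0.80) = 0.56.

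The share was 12-39% in 12 of the 16 scenarios, and 46-59% only when the risks were 5% and 80%.

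**What stratifying recovers.** Power to detect a halved NICU risk in both strata, unadjusted chi-square against Mantel-Haenszel (preterm/term):

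| Preterm share | Control NICU risk, term / preterm | Variance share | Chi-square | Mantel-Haenszel |
|---|---|---|---|---|
| 10% | 10% / 50% | 12% | 34.0% | 35.6% |
| 20% | 5% / 40% | 19% | 29.1% | 32.2% |
| 20% | 10% / 50% | 17% | 42.8% | 47.2% |
| 20% | 10% / 70% | 34% | 51.3% | 62.6% |
| 20% | 5% / 80% | 56% | 47.0% | 68.4% |
| 30% | 5% / 80% | 59% | 62.9% | 85.3% |

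The first and last rows are the smallest and largest gains among the 16 scenarios (1.6 and 22.4 points). Mantel-Haenszel type I error was 4.8-5.1%.

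**Stratify, or restrict to term?** Take 20% preterm (18 per arm, with 72 at term) and term risks of 10% versus 5%. The stratified difference weights the strata by size, 0.8 and 0.2.

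*No effect in preterm births (80% in both arms):*
- Pooled, 24% vs 20%: 0.04/√[(0.24·0.76 + 0.20·0.80)/90] = 0.65.
- Term only: 0.05/√[(0.09 + 0.0475)/72] = 1.14.
- Stratified: 0.04/√[0.64·0.1375/72 + 0.04·0.32/18] = 0.04/0.0440 = 0.91.

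*Some effect in preterm births (80% vs 65%):*
- Pooled, 24% vs 17%: 0.07/√[(0.24·0.76 + 0.17·0.83)/90] = 1.17.
- Term only: 1.14, as before.
- Stratified: 0.07/√[0.64·0.1375/72 + 0.04·0.3875/18] = 0.07/0.0456 = 1.53.

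The stratified comparison beats the pooled one in both cases. Term-only wins only if the method has no effect in preterm births, which the protocol gives no reason to assume.

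**The case against.** **The comparison is randomised.** A reader might infer that the perinatal comparison mainly measures the gestational-age mix. It does not. The mix drives the NICU rate within each arm, but 1:1 allocation balances it between arms in expectation. This part of the objection stands in full.

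**Chance imbalance is not an extra threat.** At 20% preterm, the preterm share differs between arms with an SD of √(2·0.2·0.8/90) = 6.0 points. With risks of 10% and 50%, that moves the NICU difference by an SD of 6.0 × 0.40 = 2.4 points. This might be read as a false treatment effect on top of sampling error, but it is already part of that error. The null standard error is √(2·0.18·0.82/90) = 5.7 points, and (2.4/5.7)² gives about the same 17% as the variance share above. The chi-square test allows for it; stratifying removes it.

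**This could be left to an analysis plan.** Stratified secondary analyses often are, and a plan that is not shown may contain one. Their absence is therefore not an error. The protocol does name a test for this mixed population, however, and a better one is available at no cost.

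**The gain may be small.** The live preterm share is unknown. The protocol cites guidance against inducing uncomplicated pregnancies before 41 weeks, and it excludes growth restriction, anomalies and non-reassuring fetal status. A small share, or a modest risk gap, leaves only a few points of power. The comparison may stay underpowered either way. This stands, and it limits the weight of the point.

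**Conclusion.** The point holds as a loss of precision and interpretability, minor in weight. Pooling from 28 weeks to postdates and testing without strata gives an unbiased comparison with nominal error, but leaves a known baseline predictor unused. On the assumed ranges, stratifying adds 1.6 to 22.4 points of power to detect a halved NICU risk. The true figure cannot be fixed from the protocol, because it depends on a preterm share and NICU rates that are not given.

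A reader might also conclude that term births alone should be the main perinatal comparison. The documents do not support that. Its advantage rests on assuming no effect in preterm births, and it sets aside randomised women in a trial planned by intention to treat. Restricting further to live births would condition on an event after randomisation and drop intrapartum deaths, the gravest possible harm, from the safety comparison. The primary outcome and its conclusion are unaffected.

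**What to change.** Leave eligibility, randomisation and sample size as they are. Add to the perinatal outcome definition and the analysis paragraph:

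- **Population:** all randomised women with a fetus alive at entry.
- **Deaths:** an intrapartum or early neonatal death counts as an adverse perinatal outcome and is not an exclusion.
- **Method:** compare NICU admission and low Apgar (cut-off and time of scoring to be stated) by Mantel-Haenszel, stratified by gestational age at entry, 28-36 weeks versus 37 weeks or more.
- **Reporting:** show both strata beside the combined estimate, and do not make term births alone the main comparison.

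The cost is a few sentences and one stratified table, with no new data and no more patients. Gestational age should be taken at entry, not at delivery, so that the strata are fixed before treatment. The preterm stratum may be small, so its own estimate should be read as descriptive.

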**ABSTRACT**

The World Health Organization (WHO) defines induction of labor as the initiation of labor by artificial means prior to its spontaneous onset at a viable gestational age with the aim of achieving vaginal delivery in a pregnant woman with intact membranes. Successful labor induction leads to vaginal birth while failed induction is the inability to achieve more than 3 cm cervical dilatation after 24 hours of induction of labor. In developed countries, up to 25% of term deliveries involve induction of labor compared to about 9.6% in the developing countries (6). Failed induction is an expected outcome of induction of labor. Combination methods of induction of labor may reduce the high failed induction rates reported by misoprostol or Foley catheter balloon alone.

In this study we propose a randomized trial whose aim is to find out if combined methods have a higher success rate.one arm will utilize misoprostol alone and the other combined misoprostol with Foley’s catheter. The outcomes will include successful induction, maternal and early neonatal outcomes. Failed induction or prolonged duration of induction to delivery may increase costs, patient anxiety, and if not monitored well especially in the setting of heavy workload may lead to poor neonatal outcomes.

If induction of labor using combined Foley and misoprostol can reverse or reduce these outcomes then it can change guidelines on induction of labor or for those patients at risk of failed induction.

A similar study has also not been carried out at our study setting.

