2. Induction of labor is not recommended in women with an uncomplicated pregnancy at gestational age less than 41 weeks.
3. If gestational diabetes is the only abnormality, induction of labor before 41 weeks of gestation is not recommended.
4. Induction of labor at term is not recommended for suspected fetal macrosomia.
5. Induction of labor is recommended for women with prelabour rupture of membranes at term.
6. For induction of labor in women with an uncomplicated twin pregnancy at or near term, no recommendation was made as there was insufficient evidence to issue a recommendation. If prostaglandins are not available, intravenous oxytocin alone should be used for induction of labor. Amniotomy alone is not recommended for induction of labor.

Methods of induction of labor

Methods of labor induction include mechanical and pharmacological means. Optimal choice of these depends on the pre-induction status of the cervix. The three factors most likely to lead to success include favorable cervix, multiparity and prior vaginal delivery. The cervix is considered unfavorable if the bishop score is less than 6.The most important element of bishop score is dilation, followed by effacement, station and position, with the least useful element being cervical consistency. Xenakis et al clearly demonstrated that women who had a bishop score of 3 or less at onset of induction had significantly higher rates of failed induction and caesarean delivery then those with a bishop score above 3.

Table 1-Bishop scoring system.

| Factor | 0 | 1 | 2 | 3 |
| --- | --- | --- | --- | --- |
| Dilatation (cm) | 0 | 1-2 | 3-4 | >5 |
| Effacement (%) | 0-30 | 40-50 | 60-70 | >80 |
| Consistency | Firm | Medium | Soft |  |
| Position | Posterior | Central | Anterior |  |
| Station | -3 | -2 | -1 or 0 | +1 or lower |

WHO has proposed the following recommendations,

1-If prostaglandins are not available, intravenous oxytocin alone should be used for induction of labor. Amniotomy alone is not recommended for induction of labor.

2- Oral misoprostol (25 μg, 2-hourly) is recommended for induction of labor.

3- Low-dose vaginal misoprostol (25 μg, 6-hourly) is recommended for induction of labor.

4- Misoprostol is not recommended for induction of labor in women with previous caesarean section.

5- Low doses of vaginal prostaglandins are recommended for induction of labor.

6-Balloon catheter is recommended for induction of labor.

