7-The combination of balloon catheter plus oxytocin is recommended as an alternative method of induction of labor when prostaglandins (including misoprostol) are not available or are contraindicated.

8-In the third trimester, in women with a dead or an anomalous fetus, oral or vaginal misoprostol are recommended for induction of labor.

9- Sweeping membranes are recommended for reducing formal induction of labor.

MANAGEMENT OF ADVERSE EFFECTS ASSOCIATED WITH INDUCTION OF LABOUR

Betamimetics are recommended for women with uterine hyper- stimulation during induction of labor. Uterine hyper stimulation is defined as either occurrence of uterine contractions lasting more than 60 seconds, or occurrence of more than four contractions within 10 minutes, regardless the state of the fetus.Terbutaline is the main beta mimetic used.Tocolytics like magnesium sulfate,atosiban and nitroglycerin have a small effect(3).

Setting for induction of labor

Outpatient induction of labor is not recommended for improving birth outcomes. This because induction of labor requires facilities for monitoring maternal and fetal well-being. Secondly induction should be done in a facility which has the capacity of doing a cesarean section(3).

**DEFINITION OF FAILED INDUCTION**.

Failed induction is defined as labor not starting after one cycle of treatment or after 24 hours. If induction fails, healthcare professionals should discuss this with the woman and provide support. The woman’s condition and the pregnancy in general should be fully reassessed, and fetal wellbeing should be assessed using electronic fetal monitoring. If induction fails, decisions about further management should be made in accordance with the woman’s wishes, and should take into account the clinical circumstances. The subsequent management options include: a further attempt to induce labor (the timing should depend on the clinical situation and the woman’s wishes) or caesarean section.(7). A study done by Osaheni Lucky et al. (Nigeria, 2014) found out 24.1% rate of failed induction. Locally, a study done by Esiromo (KNH, 2011) found out 26% rates of failed induction. The study also found out 77.7% success rate with misoprostol alone and 40% success with Foleys catheter alone.

**Predictors of successful induction of labor**.

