**Study population**

Pregnant women with Bishop’s score of 6 or less presenting to KNH labor wards for labor induction

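### Entry by total Bishop score admits women already above 3 cm, who could not be classed as failures if the Abstract's definition of failed induction is the primary outcome; the protocol does not say which definition applies

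*Protocol*

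**What the plan says.** **Entry.** The inclusion list under Study population reads: "Intrauterine gestation, cephalic presentation, intact membranes, IUFD and Bishop score less than 6". The shorter Study population paragraph under Methodology gives a different limit, namely women with a "score of 6 or less presenting to KNH labor wards for labor induction". Neither place, nor the exclusion list, sets a limit on dilatation itself.

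**Scoring.** The dilatation row of Table 1 in the Introduction is "Dilatation (cm) | 0 | 1-2 | 3-4 | >5", scored 0, 1, 2 and 3 points.

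**Outcome.** The Outcomes section says only "Primary outcome-failed induction". The analysis paragraph names failed or successful induction, again without a definition. Two definitions appear elsewhere:

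- Abstract: "failed induction is the inability to achieve more than 3 cm cervical dilatation after 24 hours of induction of labor".
- Introduction, under its own heading on the definition of failed induction: "Failed induction is defined as labor not starting after one cycle of treatment or after 24 hours".

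**Analysis and size.** The analysis is by intention to treat, with a chi-square comparison of proportions. The sample size is 90 per group for 80% power at two-sided 0.05: "Where we define p_c_=74% and p_a_=90% to be the proportions of women in the misoprostol and combined misoprostol and Foley groups respectively".

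**The concern.** A threshold endpoint works only if participants start on the wrong side of the threshold. The total Bishop score does not guarantee this, because dilatation is one of five components and a low score on the others can offset it. If the 3 cm rule is the endpoint, a woman who enters at 4 cm is counted as not failed whatever she is given. She stays in the intention-to-treat comparison and carries no information on the protocol's question, which is about cervical ripening and induction.

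Such women pull the failure rate down by the same proportion in both arms, so the absolute difference shrinks. The planned sample size has almost no reserve to absorb that.

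**Working it through.** **1. Can a woman above 3 cm be eligible?** Inputs: Table 1 and the two entry limits. Take 4 cm (2 points), effacement 40-50% (1), firm cervix (0), posterior position (0), station -2 (1). The total is 2 + 1 + 0 + 0 + 1 = 4, which satisfies both limits.

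More generally, the other four components take 4 × 3 × 3 × 4 = 144 combinations (effacement 0-3, consistency 0-2, position 0-2, station 0-3). The number of combinations summing to 0, 1, 2, 3 and 4 is 1, 4, 10, 18 and 25.

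| Dilatation category | Total below 6 | Total 6 or below |
| --- | --- | --- |
| 3-4 cm (2 points) | others at most 3: 33 of 144 | others at most 4: 58 of 144 |
| over 5 cm (3 points) | others at most 2: 15 of 144 | others at most 3: 33 of 144 |

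These are cells of a table, not frequencies of patients. The 3-4 cm category also contains women at exactly 3 cm, who have not passed the threshold. The count shows only that the entry rule does not keep women above 3 cm out.

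**2. Would she be counted as not failed?**

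| Definition | Woman at 4 cm, not in labour, at entry |
| --- | --- |
| Abstract: not more than 3 cm after 24 hours | Threshold already passed; cannot be classed as a failure |
| Introduction: labour not starting after one cycle or 24 hours | Can still fail |

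The Outcomes section and the analysis paragraph assign neither.

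**3. The plan's own sample size.** With success rates 0.74 and 0.90, mean 0.82 and difference 0.16:

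n = [1.96 √(2 × 0.82 × 0.18) + 0.84 √(0.74 × 0.26 + 0.90 × 0.10)]² / 0.16²
= [1.065 + 0.446]² / 0.0256 = 89.2, so 90 per group.

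The stated figure reproduces. Power at n = 90:

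Φ{[0.16 √90 − 1.96 √0.2952] / √0.2824} = Φ{(1.518 − 1.065) / 0.531} = Φ(0.852) = 80.3%.

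**4. Dilution, if the Abstract's definition applies.** Let f be the share of randomised women already above 3 cm. The protocol gives no value, so f is an assumption. Suppose also that 26% and 10% are the failure rates among women not past 3 cm. The expected rates become 0.26(1 − f) and 0.10(1 − f), and the same power formula gives:

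| f | Failure, misoprostol | Failure, combined | Difference (points) | Power at 90 per group | n per group for 80% |
| --- | --- | --- | --- | --- | --- |
| 0 | 26.0% | 10.0% | 16.0 | 80.3% | 90 |
| 2% | 25.5% | 9.8% | 15.7 | 79.3% | 92 |
| 5% | 24.7% | 9.5% | 15.2 | 77.8% | 96 |
| 10% | 23.4% | 9.0% | 14.4 | 75.0% | 102 |
| 20% | 20.8% | 8.0% | 12.8 | 68.9% | 117 |

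The rates used are those from which the 90 per group was computed. The same section also says "We postulate that offering a combined use of misoprostol and Foley catheter will reduce this proportion to 16" per cent, which does not match a 90% success rate. That is a separate inconsistency and is not pursued here.

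**The case against.** A reader might infer that women at 4 cm simply cannot fail the primary outcome. The protocol does not support that without qualification. The definition with its own heading in the Introduction turns on labour starting, and under it such a woman can fail. The Abstract itself ties successful induction to vaginal birth, which she has not achieved at entry either. This objection stands: the overlap between entry and endpoint depends on the definition chosen.

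Four further objections have force.

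- **The share affected is unknown.** Nothing in the protocol supports any particular f, least of all the 20% row. Reading 33 of 144 as a proportion of patients would be a mistake.
- **The 26% may already include such women.** It comes from an earlier study at the same hospital, and the protocol reports no dilatation limit for it. If those women were in that study, multiplying by (1 − f) discounts the rate twice and the loss of power is smaller than tabulated.
- **Randomisation is 1:1.** The expected effect is dilution and lost power, not bias. A chance imbalance in these women is possible, as it is for any prognostic factor.
- **Women in labour are largely outside the population anyway.** The Abstract and Introduction describe induction as preceding spontaneous labour, so a separate exclusion for active labour would add little. This does not, however, exclude a woman at 4 cm who is not in labour.

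It is also tempting to argue from its 30 cc volume that the balloon could not stay in place at 4 cm. The protocol says nothing on retention at a given dilatation, and the point does not need it.

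None of this removes the two facts that remain: the entry rule admits women above 3 cm, and one of the two stated definitions makes them automatic non-failures.

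**Conclusion.** The concern holds in a conditional form. Entry is not limited by dilatation, and Table 1 allows a total score of 4 at 4 cm. If failed induction is judged by the Abstract's 3 cm rule, women above 3 cm at entry are fixed as non-failures in both arms and dilute the primary comparison. If it is judged by the Introduction's rule, they are not. The protocol leaves this open.

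The likely size is modest: power of about 78% if 5% of women are affected and 75% if 10% are, against 80% as planned. These figures rest on an assumed share and on reading 26% and 10% as rates among women not already past 3 cm. Women at exactly 3 cm are unaffected. The point is worth acting on because it concerns the primary outcome, the design has almost no power to spare, and the repair is small.

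**What to change.** 1. Reconcile the Abstract and the Introduction into one operational definition of failed induction, and state it in the Outcomes section as the primary outcome.
2. If the 3 cm threshold is kept, make the inclusion criteria consistent with it, so that women already above 3 cm at baseline are not enrolled. The limit need be no tighter than the endpoint threshold: a 2 cm ceiling would also remove women at 3 cm, who can still fail. Settle the two Bishop limits (below 6, or 6 and below) in the same edit.
3. Record baseline dilatation as its own item, before the allocation envelope is opened. It has to be assessed to score the Bishop, but the protocol does not say that the component is kept.
4. If enrolment has begun, add a sensitivity analysis of the primary outcome without women above 3 cm at baseline. Because the subset is defined by a pre-randomisation measurement, the comparison between arms remains a randomised one.

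The cost is an outcome definition, one eligibility line and one data item. A few women would no longer be eligible, and recruitment would slow slightly.
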